# *Atmiyata,* a community-led intervention to address common mental disorders: Study protocol for a stepped wedge cluster randomized controlled trial in rural Gujarat, India

**DOI:** 10.1186/s13063-020-4133-6

**Published:** 2020-02-21

**Keywords:** Stepped wedge cluster randomised controlled trial, Community-led intervention, Community mental health, Low-and-middle-income countries, Evidence-based practice, Common mental disorders

## Abstract

**Background:**

While lay-health worker models for mental health care have proven to be effective in controlled trials, there is limited evidence on the effectiveness and scalability of these models in rural communities in low- and middle-income countries (LMICs). *Atmiyata* is a rural community-led intervention using local community volunteers, called Champions, to identify and provide a package of community-based interventions for mental health, including evidence-based counseling for persons with common mental disorders (CMD).

**Methods:**

The impact of the *Atmiyata* intervention is evaluated through a stepped wedge cluster randomized controlled trial (SW-CRCT) with a nested economic evaluation. The trial is implemented across 10 sub-blocks (645 villages) in Mehsana district in the state of Gujarat, with a catchment area of 1.52 million rural adults. There are 56 primary health centers (PHCs) in Mehsana district and villages covered under these PHCs are equally divided into four groups of clusters of 14 PHCs each. The intervention is rolled out in a staggered manner in these groups of villages at an interval of 5 months.

The primary outcome is symptomatic improvement measured through the GHQ-12 at a 3-month follow-up. Secondary outcomes include: quality of life using the EURO-QoL (EQ- 5D), symptom improvement measured by the Self-Reporting Questionnaire-20 (SRQ-20), functioning using the World Health Organization’s Disability Assessment Scale (WHO-DAS-12), depression symptoms using the Patient Health Questionnaire (PHQ-9), anxiety symptoms using Generalized Anxiety Disorder Questionnaire (GAD-7), and social participation using the Social Participation Scale (SPS). Generalized linear mixed effects model is employed for binary outcomes and linear mixed effects model for continuous outcomes. A Return on Investment (ROI) analysis of the intervention will be conducted to understand whether the intervention generates any return on financial investments made into the project.

**Discussion:**

Stepped wedge designs are increasingly used a design to evaluate the real-life effectiveness of interventions. To the best of our knowledge, this is the first SW-CRCT in a low- and middle-income country evaluating the impact of the implementation of a community mental health intervention. The results of this study will contribute to the evidence on scaling-up lay health worker models for mental health interventions and contribute to the SW-CRCT literature in low- and middle-income countries.

**Trial registration:**

The trial is registered prospectively with the Clinical Trial Registry in India and the Clinical Trial Registry number- CTRI/2017/03/008139. URL http://ctri.nic.in/Clinicaltrials/regtrial.php?modid=1&compid=19&EncHid=70845.17209. Date of registration- 20/03/2017.

## Background

Mental illness is a substantial public health burden in India, affecting 10.6% of the population [1]. There is a shortage of mental health professionals to address the mental health needs of the population, particularly in rural areas [1]. This is further compounded by a high level of public stigma towards mental illness and the lack of accessible mental health care, resulting in a treatment gap of nearly 80–90% for mental illness in India [1].

In most low- and middle-income countries (LMICs), service delivery models have focused on task-sharing, the process of sharing mental health care tasks with less specialised health workers, such as community health workers [2]. Several programs have been developed to build the capacity of community members and primary care health workers, with the aim of increasing their uptake of mental health tasks and enable access to mental health supports in rural areas [3, 4]. A number of studies in India and other parts of South Asia have shown the efficacy of task-sharing initiatives [5–8].

A possible reason for the inability to scale-up task-sharing models may be that public health systems in low-and-middle-income countries (LMICs) are overburdened with addressing other health needs, and there are limited time and energy to devote to mental health [9–12]. Task sharing approaches may, therefore, need to build community capacity to provide mental health care that complements service provision efforts within the public health system. *Atmiyata* is a community-led intervention [13] using non-specialised community volunteers for identification, support, and referral for persons with common and severe mental disorders. *Atmiyata* was previously piloted in 41 villages in the Nashik district of the state of Maharashtra from 2013 to 2015 [13].

As a mental health program, *Atmiyata* aims to: (i) reduce the treatment gap for common and severe mental disorders; (ii) improve mental health outcomes for people with common mental disorders (CMD); (iii) improve quality of life among people with mental health problems; (iv) improve access to social welfare schemes for people with mental health problems. We hypothesize that the intervention will result in symptomatic improvement in CMD (depression and anxiety) and well-being as well as narrow the mental health ‘care’ gap [14]. Evaluating both the efficiency as well as the implementation process of this intervention will generate valuable lessons as to how we might sustain the intervention’s impact when delivered to a large population.

## Methods

### Design

We employ a Stepped Wedge Cluster Randomized Controlled Trial (SW-CRCT), with a nested health economic evaluation to assess the impact on persons with CMD and return on investment (ROI) of the intervention in the Indian state of Gujarat. The stepped wedge design is chosen for evaluating the scale-up of *Atmiyata* intervention as it allows for random allocation of the timing in which clusters receive the intervention [15]. All clusters receive the intervention before the trial ends which is ethically appropriate. The design also allows for *Atmiyata* intervention to be delivered in a staggered manner to account for practical logistics constraints; it is not feasible to deliver the intervention in all clusters (villages served under groups of primary health centers) simultaneously. Stepwise implementation allows the implementation team enough preparation time and is an efficient use of implementation team resources. Additionally, the staggered implementation of the intervention over time periods allows for more in-depth statistical analysis compared to a pre-post, parallel-arm cluster randomized controlled trial design.

There are 56 primary health centers (PHCs) in the Mehsana district (where the study takes place), and each PHC serves discrete villages within a geographical area. Each village in the geographical area served by a PHC is a cluster in this study. We created 4 groups of clusters (A, B, C, D), each made up of villages covered by 14 PHCs. Groups are created according to geographical location to help reduce the probability of contamination between groups; villages in Group A are farther from Group B villages and villages in Group C are farther from Group D. All groups (A, B, C, D) are allocated to intervention condition at different steps. A ‘Step’ is the order in which a group of clusters switches from control to intervention condition. On the other hand, ‘Period’ is defined as a group of observations by the time of measurement. The duration of each period is 5 months to accommodate for baseline and 3 months of follow-up data collection (Fig. 1).

**Fig. 1 Fig1:**
[figure not shown]
SPIRIT figure. Enrollment, allocation, intervention, and assessment were taken place in all periods as this is a cross-sectional SW-CRCT

This study uses a repeated cross-sectional design with outcome data derived from different participants in each period. All four clusters start at baseline in the control condition and are exposed to the intervention at a regular period of five months (Fig. 1).

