### Primary outcome

The primary outcome is the symptomatic improvement of CMD as measured using a validated Gujarati version of the GHQ-12 [18] from baseline to 3-month and 8-month follow-up to evaluate sustained effects of the intervention. The GHQ-12 is a widely used screening tool with reliable sensitivity for assessing CMD [19]. GHQ-12 is a dichotomous 12-item questionnaire with each item rated on a 4-point scale, with possible responses being “less than usual,” “no more than usual,” “rather more than usual,” or “much more than usual.” We used a bimodal scoring method, whereby “less than usual” and “no more than usual” is scored as 0 point, and “rather more than usual” and “much more than usual” is scored as 1 [18]. GHQ-12 scores will be analyzed as both continuous (ranging from 0 to 12) and categorical outcomes (case defined as 3 and above scores on GHQ scale; non-case as less than 3 scores on GHQ scale).

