Costs are calculated using both government and societal perspective [29]. Perspective determines the cost components to be included in any cost analysis and societal perspective is the broadest viewpoint that covers all costs irrespective of who incurs these costs. On the other hand, a government perspective only includes costs incurred by the government for a particular health intervention. Costs are accounted under two categories: 1. total cost of the intervention and; 2. treatment cost of CMDs. Treatment costs are categorized as: direct medical cost, direct non-medical cost, and indirect costs. Direct medical costs include out of pocket expenses incurred in order to seek treatment (e.g. diagnostic tests, fees for consultation in clinics, traditional healers, hospitals, bed day charges at a public or private health facility). Direct non-medical costs include the amount spent for travelling to the health facility for the patient and accompanied persons for treatment, the amount spent on meal/food taken while waiting for treatment, expenses for overnight accommodation for seeking care, etc. Indirect costs represent the opportunity cost for the patient and their household members’ time related to CMD. Cost data is collected at baseline, 3 months and 8 months from all study participants. Time spent by the champion will be obtained from the program implementation data. The minimum wage rate of Gujarat will be used to value their time. Total hours spent on the program will be multiplied by hourly wage (obtained from the minimum wage rate) to get the time cost of the Champions. Benefits are considered in terms of improved health, functioning, participation, productivity, increased saving and investment, reduced informal care giving and health and welfare services. Lost workdays before and after the intervention will be obtained through the WHO-DAS 12 questionnaire and will be linked to the minimum wage rate to estimate the aggregate effect. Being alive and healthy is also considered valuable and the overall value of a life year can be broken down into its economic (instrumental) and health (intrinsic) elements. Following the approach used in prior ROI analyses in mental health, we use the figure of 0.5 times the per-capita income of India as the value of a healthy life year [28, 30, 31].

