### Sample size and power calculations

A trained lay health worker-led intervention study conducted in India reported a risk difference of 12% at follow up between intervention and control condition for the recovery of CMD patients [5, 37]. The sample size for this SW-CRCT is calculated to detect a 13% difference in CMD cases at a 3-month follow-up using GHQ-12 as a categorical measure between the intervention (58% improved) and control condition (45% improved). Assuming an intra-cluster correlation coefficient of ICC = 0.1, number of steps (t = 4), number of clusters randomized in each step (k = 14), average cluster size (m = 4), power (80%) and alpha of 0.05, a sample size of 1120 participants is needed, with approximately 56 individuals per cluster per period (Fig. 1, 3). The sample size was calculated using the “stepped wedge” function of STATA version 14 [38].

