### Randomization and treatment allocation

The unit of randomization in stepped wedge trials is a cluster or group of clusters, allocated to different steps. In India, PHCs serve discrete villages and hence we have used the PHC as a unit to identify discrete geographical areas consisting of all villages under a PHC. This geographical area is taken as a cluster for our study. Typically, a PHC in Gujarat covers a population of 25,000–30,000 across 12–13 villages. There are 56 PHCs in the Mehsana district, split into 4 groups (A, B, C, D), with each group consisting of all villages under 14 PHCs. These groups of clusters (A, B, C, D) are sequentially allocated to different steps at given time periods. Randomization takes place at the level of participants, all the participants are randomly selected for each period from each of these groups of clusters (A, B, C, D) as described in the recruitment section below. The administrative organization of primary health care in Gujarat ensures that the inter-PHC movement of people for health care is minimal and avoids contamination of the intervention. Since double-blinding is not possible in such psychosocial intervention trials, several other procedures are used to minimize contamination and bias. To minimize contamination due to the intervention and control village members meeting and potentially discussing the intervention, clusters are geographically dispersed. Second, the data collection team is separate from the intervention team and blind to the treatment status. Third, the data collection staff receives initial training and re-training at repeated intervals to ensure the quality of data collected.

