### Statistical analysis

Baseline characteristics will be summarized using counts (percentages) for categorical variables and means (SD) for continuous variables. The analysis will be based on intention to treat and participants will be analyzed in the group that the cluster was assigned to at each time point.

The analysis plan is based on the Hussey and Hughes model for the analysis of cross-sectional SW-CRCT designs [15]. Generalized Linear Mixed Model (GLMM) will be used to determine the size and direction of the difference between the control and intervention conditions for primary and secondary outcomes. The estimated intervention effect will be reported as the mean outcome difference for continuous variables and Odds Ratio for categorical variables between intervention and control condition assuming a constant treatment effect over time. Estimates of the difference and 95% CIs will be calculated. To take the time effect into account, all analyses will be adjusted for time (periods) of the intervention and clusters. Period (time) and intervention (counseling sessions) will be specified as fixed effects and clusters as a random effect. The analysis will be adjusted for baseline covariates to account for potential imbalance arising due to different recruitment procedures and regional differences across control and intervention conditions. The analysis plan does not include any interim analyses.

Two broad model extensions [41], random cluster by period effect and random cluster by treatment effect will be used for secondary analysis. The secondary analysis will investigate an interaction effect between intervention and time and the interaction effect between cluster and time. Additional analyses of the primary outcome will be conducted controlling for demographic variables if required. Statistical analyses will be carried out using STATA version 14 [38].

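### The 8-month visit outlasts the 5-month step, so 40% of controls are seen at 8 months after their villages have crossed over, and the analysis rule does not say how to classify them

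*Protocol article*

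**What the plan says.** All references are to the Protocol article.

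- **Crossover schedule** (text under Fig. 1): "All four clusters start at baseline in the control condition and are exposed to the intervention at a regular period of five months". Randomization and treatment allocation adds: "These groups of clusters (A, B, C, D) are sequentially allocated to different steps at given time periods".
- **Period length** (Design): "The duration of each period is 5 months to accommodate for baseline and 3 months of follow-up data collection".
- **Primary outcome**: GHQ-12 improvement "from baseline to 3-month and 8-month follow-up to evaluate sustained effects of the intervention". The Abstract and the sample size section name 3 months only.
- **Who is seen at 8 months**: Table 1 limits only the satisfaction questionnaire to the intervention condition. Economic Evaluation says: "Cost data is collected at baseline, 3 months and 8 months from all study participants". Controls therefore have 8-month visits.
- **Analysis rule** (Statistical analysis): "participants will be analyzed in the group that the cluster was assigned to at each time point".
- **Size** (Sample size and power calculations): "a sample size of 1120 participants is needed, with approximately 56 individuals per cluster per period". Here 56 is the number per group of 14 PHCs, that is 14 x 4.

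**The concern.** The period was sized to hold the baseline and the 3-month visit. The 8-month visit does not fit in it. For the cohort recruited just before crossover, that visit comes when Champions are already working in the same villages. These participants scored 3 or more on the GHQ-12, so they belong to the population that Champions look for, and the Recruitment section states no exclusion of former controls. The contamination safeguard described is geographical separation, which does nothing about the same village changing condition over time. The Discussion names the recruitment difference as a confounder but not this overlap.

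The analysis rule can be read in two ways. If the time point is the recruitment period, these people are controls who may have been exposed. If it is the visit date, people drawn from the electoral roll and given enhanced usual care become intervention participants at 8 months. The two readings can give very different estimates. The 8-month GHQ-12 result, the 8-month secondary outcomes and the 8-month cost data all depend on the choice. A weak 8-month result could also be misread as an effect that fades.

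**Working it through.** **1. Reproducing the plan's sample size.** Inputs from Sample size and power calculations: 45% v 58%, ICC 0.1, 4 steps, 14 clusters per step, 4 per cluster per period, 80% power, alpha 0.05 (two-sided assumed).

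- Individually randomised size: 231 per arm (228 with unpooled variance).
- Stepped-wedge design effect (Woertman): [1 + 0.1(16 + 4 - 1)] / [1 + 0.1(8 + 4 - 1)] x 3(0.9) / [2(4 - 1/4)] = (2.9/2.1) x 0.36 = 0.497.
- Total over 5 periods: 2 x 231 x 0.497 x 5 = 1148, or 1134 unpooled, against the stated 1120.
- The Hussey-Hughes variance at N = 1120 gives SE 0.047 and about 79% power.

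The stated figure is reproduced to within 3%, so the layout is 4 groups by 5 periods (1120 / (4 x 56) = 5).

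**2. How many controls are affected.** With one group crossing per step, the groups have 1, 2, 3 and 4 control cells, 10 in all, or 10 x 56 = 560 controls. Each group has one last control cell: 4 x 56 = 224, and 224/560 = 40%. The first group to cross has only that one cell.

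**3. When they are seen.** Let r be the month of recruitment within the period. Crossover is at month 5 and the 8-month visit is at month r + 8, so the visit is r + 3 months after crossover. For the 3-month visit to fit in the period, r is at most 5 - 3 = 2, giving 3 to 5 months after crossover for every such control. The cohort one period earlier crosses at month 10 and is seen by month 10, so it adds none. If recruitment filled all 5 months, 3/5 of that earlier cohort (three cells) would be added: (4 + 3 x 0.6)/10 = 58%. So 40% is the lower figure. The recruitment dates in Trial status (April 2017 to August 2019, about 29 months) would allow 29/5 = 5.8 months per period. That is still shorter than 8.

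**4. Possible dilution.** Assume a fraction c of the true effect reaches these four cells by 8 months. In the Hussey-Hughes estimate (linear scale, ICC 0.1) their weights are -0.114, -0.176, -0.238 and -0.300, with sum -0.829. The expected estimate for a true 13 points, analysed by recruitment period, is 13 x (1 - 0.829c):

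| c (assumed) | Expected estimate |
|---|---|
| 5% | 12.5 |
| 10% | 11.9 |
| 25% | 10.3 |

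The weight depends on the ICC: the sum is -0.75 at ICC 0.05 and -0.64 at ICC 0.01.

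**5. The other reading of the rule.** If the four cells are coded as intervention at 8 months, the same model gives 2.8 points at c = 5% and 4.9 at c = 25%. At low uptake the choice of label matters far more than the dilution in step 4.

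**6. Precision without these cells.** Removing them raises the SE from 0.047 to 0.065.

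**The case against.** The main analysis is protected. The Abstract, the sample size and the period length all rest on 3 months, and the 3-month visit falls inside the period. That stands, and it limits the point to the 8-month results.

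Being seen after crossover is not the same as being treated. To receive the counselling effect, a former control must be found by a Champion and receive 4-6 sessions over 6-12 weeks, all within 3-5 months. The films, by the protocol's own account, were not designed to reduce symptoms. Uptake may therefore be low. This also stands, and for that reason c is shown as a range.

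Handling of late visits is often left to an analysis plan, which is not shown. That carries less weight here, because the article does state a rule and the rule has two readings with different consequences.

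A reader might also infer stronger claims that the documents do not support:

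- *The 8-month effect is biased towards zero.* This mechanism dilutes only if the intervention helps and some of its effect reaches these controls. The recruitment routes also differ (electoral roll v Champion caseload), a separate bias of unknown direction.
- *The model relies most heavily on exactly these cells.* The first-crossing group's last control cell has weight -0.114, smaller in size than a control cell of the last group that is not next to crossover (-0.162). First intervention cells carry weights as large as 0.300.
- *Power at 8 months is 52% instead of 80%.* The plan claims 80% at 3 months only. The 52% arises only if these cells are excluded and 13 points is assumed at 8 months.
- *These controls must be excluded.* Taking bias and SE together, root-mean-square error is 4.8 points keeping them v 6.5 dropping them at c = 10%, and 5.4 v 6.5 at c = 25%. Exclusion does better only above c of about 41%. It also removes every control of the first-crossing group.
- *Intention to treat fails on either reading.* Classifying by condition at recruitment is ordinary intention to treat. It may be diluted, but it does not fail.

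**Conclusion.** The point holds for the 8-month results. On the stated schedule, 224 of 560 controls (40%) have their 8-month visit at least 3 months after their villages cross over, and the analysis rule leaves their condition open. Classified by recruitment period, dilution of a true 13 points would be about 0.5 points at c = 5%, 1.1 at 10% and 2.7 at 25%.

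This rests on four assumptions: c, which the documents do not give; a true 13-point effect at 8 months, borrowed from the 3-month sample size; ICC 0.1; and a linear approximation to the planned mixed model. The timing and the 40% rest on none of these, only on the planned 5-month steps and equal cells of 56. The net direction of bias at 8 months is not established. The 3-month result and its sample size stand.

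**What to change.** 1. **Primary outcome:** name 3 months as the only primary time point, in line with the Abstract and the sample size section, and make 8 months secondary.
2. **Statistical analysis:** define each participant's condition, for all visits, as the condition of the group in the period of recruitment.
3. **8-month clinical and cost analyses:** specify, before the 8-month results are seen, a sensitivity analysis that excludes the last pre-crossover control cohort or gives it its own model indicator. State that the main 8-month estimate may be diluted.

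No new data are needed. The cost is a little more analysis work and a less precise sensitivity estimate (SE about 0.065 v 0.047 on the plan's own assumptions).
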